## Withdrawal of individual subjects

Subjects can leave the study at any time for any reason if they wish to do so without any consequences. The investigator can decide to withdraw a subject from the study for urgent medical reasons (see chapter 4.4).

### Specific criteria for withdrawal

See chapter 4.4

## Replacement of individual subjects after withdrawal

Subjects who withdraw during the first two weeks will try to be replaced. Subjects who will drop-out during a later time in the trial will not be replaced.

## Follow-up of subjects withdrawn from treatment

When a subject is withdrawn prematurely from the study, proper follow up will be given if necessary.

## Premature termination of the study

In case of premature termination/suspension of the trial for any reason, the investigator will inform:

- the regulatory authorities (if applicable)
- the trial subject, assuring him/her appropriate treatment and follow up

If the investigator terminates or suspends the trial without prior agreement of the sponsor, then the institution should:

- promptly inform and provide the sponsor and the METC with a detailed written explanation of the termination or suspension.

If the sponsor terminated/suspends the trial, then the institution will:

- promptly inform and provide the METC with detailed written explanation of the termination or suspension.

If the METC terminates or suspends its approval of the trial, then the institution will:

- promptly notify and provide the sponsor with a detailed written explanation of the termination or suspension.

# SAFETY REPORTING

## Section 10 WMO event

In accordance to section 10, subsection 1, of the WMO, the investigator will inform the subjects and the reviewing accredited METC if anything occurs, on the basis of which it appears that the disadvantages of participation may be significantly greater than was foreseen in the research proposal. The study will be suspended pending further review by the accredited METC, except insofar as suspension would jeopardise the subjects’ health. The investigator will take care that all subjects are kept informed.

## Adverse and serious adverse events

An adverse event is defined as any undesirable experience occurring to a subject during a clinical trial, whether or not considered related to the clinical trial.

The medical occurrence is untoward in frequency and/or kind. An Adverse Event can be any unfavourable or unintended phenomenon (including abnormal laboratory values), every symptom that or every illness that is time-related to the use of an investigational product, either or not related to the intake of this investigational product.

At every study visit the subjects will be asked about their well-being and the experience of any adverse event.
Details of all adverse events reported spontaneously by subjects or observed by the investigator or medical staff will be recorded in appropriate adverse event report forms and reported to the principal investigator and the responsible medical doctor. All adverse events observed will be recorded separately.

A serious adverse event is any untoward medical occurrence or effect that at any dose results in death:

- is life threatening (at the time of the event);
- requires hospitalisation or prolongation of existing inpatients’ hospitalisation;
- results in persistent or significant disability or incapacity;
- is a new event of the trial likely to affect the safety of the subjects, such as an unexpected outcome of an adverse reaction, lack of efficacy of an IMP used for the treatment of a life threatening disease, major safety finding from a newly completed animal study, etc.

All SAEs will be reported to the METC of Maastricht University, which approved the protocol, according to the requirements of the METC.

## Follow-up of adverse events

All adverse events will be followed until they have abated, or until a stable situation has been reached. Depending on the event, follow up may require additional tests or medical procedures as indicated, and/or referral to the general physician or a medical specialist.

# STATISTICAL ANALYSIS

## Descriptive statistics

All normally distributed data will be presented as mean ± standard deviation (SD). If data are not normally distributed the median and 25th-75th percentiles will be given.

This approach will be applied to the baseline characteristics of the study population as well as to the primary and secondary study parameters.

## Univariate analysis

Differences in baseline characteristics between the subjects will be assessed by a parametric test (independent-samples Student’s t-test), if data are normally distributed. In case of non-normality, data will be transformed to obtain a normal distribution. However, if this transformation will not be successful, differences will be tested by the nonparametric Mann-Whitney U-test.

**Other study parameters**

The individual changes from baseline in each of the other parameters (secondary study parameters # 4-6 and other study parameters # 1-4) assessed will be calculated separately for the 4-week intervention interval and the 8-week intervention interval. If data are normally distributed, significant different alterations between the verum and the placebo group will be appraised per study parameter by independent-samples Student’s t-test.

In case data will not be distributed normally, transformation will be performed to achieve normal distribution. If transformation remains unsuccessful, Mann-Whitney U-test will be used for the analyses.

All tests will be carried out two-sided. Statistical significance will be accepted at the 95% confidence level (p ≤ 0.05).

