## Sample size calculation

There are currently no suitable data available that allow a persuasive sample size calculation for the effects of the 8 weeks consumption of the OPC extract assessed by either FMD or LDF. Due to this limitation the present study is considered as a pilot study to proof the concept and provide - among others - data for a power calculation required for a larger intervention study.

However, by recruiting the initially projected 34 subjects (17 subjects per test group under taking into account a drop-out rate of 10 %) and assuming a variance (σ) of 1.8 % for the change in brachial FMD (calculated as the change from baseline in diastolic diameter divided by the change from baseline in mean blood flow velocity), we are able to detect a change of 1.4 % in brachial FMD in a group of n = [2  (z + z)2/(µx - µy)2 = 15 subjects with a power of 80% ( = 0.20; z= 0.84) and an -value of 0.05 (z 1.96) upon the OPC treatment.

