## Multivariate analysis

Multivariate analyses are not intended to be performed.

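### Section 9.2 compares the markers as unadjusted changes from baseline; adjusting for the visit 2 value is more precise unless r exceeds about 0.9, and it removes the shift from chance baseline imbalance

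*Protocol*

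**What the plan says.** Section 9.2, under Other study parameters, takes "The individual changes from baseline in each of the other parameters", separately for the 4-week and 8-week intervals. If the data are normal, "significant different alterations between the verum and the placebo group will be appraised per study parameter by independent-samples" t-test. If not, the data are transformed, and failing that, "If transformation remains unsuccessful, Mann-Whitney U-test will be used for the analyses". No step uses the baseline value as a covariate. On level and sidedness the section says "All tests will be carried out two-sided. Statistical significance will be accepted at the 95% confidence level (p ≤ 0.05").

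Section 9.3 adds: "Multivariate analyses are not intended to be performed". That heading could strictly refer to joint analysis of several outcomes. Beside a section 9.2 that names only two-sample tests, the natural reading is that covariate models are excluded too. On either reading none is planned.

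The rule's stated scope is "secondary study parameters # 4-6 and other study parameters # 1-4". The secondary lists in the Summary and in section 7.1.2 stop at item 3, and the secondary objectives in section 2 stop at item 4, so the reference does not match the list it points to. The phrase about each of the other parameters suggests that all non-vascular markers are meant.

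Section 7.2 balances the groups on two classes of cigarettes per day and on no marker.

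**The concern.** Subtracting the baseline fixes its slope at 1. When baseline and follow-up have similar spread, the slope that minimises the variance is about r, so subtraction over-corrects whenever r is below 1. This has two consequences.

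- The treatment comparison is noisier than it needs to be. With about 15 men per group there is little precision to spare.
- If one group starts high on a marker by chance, it will tend to show a larger fall through regression to the mean, and the unadjusted comparison of changes attributes that fall to treatment.

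Section 4.5 describes the trial as a pilot meant to supply data for a later power calculation. Efficient marker estimates, adjusted for imbalance, serve that purpose directly.

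**Working it through.** **Inputs**

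- Evaluable men per group: 15. Section 4.5 gives "17 subjects per test group under taking into account a drop-out rate of 10" per cent, and 17 × 0.90 = 15.3.
- Two-sided alpha 0.05 (section 9.2).
- Correlation r between the visit 2 value and the follow-up value of a marker: not in the protocol. Assumed, and shown from 0.2 to 0.9, with equal SD at both visits.
- Effect for the power illustration: 1 between-subject SD. Assumed; the protocol states no power for any marker.

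**The plan's own figure first.** Section 4.5 derives 15 per group for brachial FMD, "assuming a variance (σ) of 1.8 % for the change in brachial FMD". With 1.8 taken as the variance, n = 2 × 1.8 × (1.96 + 0.84)² / 1.4² = 14.4, rounded up to 15; 15 / 0.90 = 16.7, rounded up to 17 per group and 34 in total. The 15 reproduces on that reading. Taking 1.8 as the SD gives 25.9. The variance ratios below do not depend on which reading is right.

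**Formulas.** In units of the variance from comparing follow-up values alone:

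- change score: 2(1 - r)
- ANCOVA, large sample: 1 - r²
- ratio ANCOVA / change: (1 - r²) / [2(1 - r)] = (1 + r)/2
- cost of estimating the slope with 30 men: a factor of about 1 + 1/26 = 1.038
- shift of the change comparison given a baseline difference d0: -(1 - r) × d0
- standard error of d0 with 15 per group: √(2/15) = 0.365 SD

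Power is from the noncentral t distribution: 28 df for the change score, 27 df and the 1.038 factor for ANCOVA.

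| r | change 2(1-r) | ANCOVA 1-r² | ratio | ratio × 1.038 | power, change | power, ANCOVA | shift at d0 = 0.365 SD |
|---|---|---|---|---|---|---|---|
| 0.2 | 1.60 | 0.96 | 0.60 | 0.62 | 55% | 75% | -0.29 SD |
| 0.3 | 1.40 | 0.91 | 0.65 | 0.67 | 61% | 78% | -0.26 SD |
| 0.5 | 1.00 | 0.75 | 0.75 | 0.78 | 75% | 85% | -0.18 SD |
| 0.7 | 0.60 | 0.51 | 0.85 | 0.88 | 93% | 95% | -0.11 SD |
| 0.8 | 0.40 | 0.36 | 0.90 | 0.93 | 98.7% | 99.1% | -0.07 SD |
| 0.9 | 0.20 | 0.19 | 0.95 | 0.99 | about 100% | about 100% | -0.04 SD |

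Comparing follow-up values alone gives 75% power throughout.

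**Break-even points.** Setting 1.038 × (1 + r)/2 = 1 gives r = 0.93, so ANCOVA's advantage is lost only above about 0.9. Setting 2(1 - r) = 1 gives r = 0.5; only below that is the change score also less precise than ignoring baseline.

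**Simulation under no effect** (15 per group, 100,000 trials at each of r = 0.3, 0.5 and 0.7). The mean change-score difference was about 0, and type I error over all trials was 4.9 to 5.0%. ANCOVA variance exceeded its large-sample value by 3 to 4%, in line with the 1.038 factor. Among trials whose baseline difference exceeded 0.5 SD in either direction, the change-score test rejected in 14% (r = 0.3), 12% (r = 0.5) and 9% (r = 0.7). Such a difference is 0.5 / 0.365 = 1.37 standard errors, which arises in about 17% of randomisations for any one marker.

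**The case against.** The strongest defence is that the planned test is valid. It is prespecified, keeps its level, is unbiased over randomisation, and concerns secondary and exploratory markers in a pilot for which no marker power is claimed. All of that stands, and it makes this an improvement in efficiency rather than the correction of an invalid test.

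Several stronger readings are tempting, and the protocol does not support them.

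- **That the change score is worse than ignoring baseline.** This is true only for r below 0.5. The protocol gives no correlation for any marker. High variability does not settle the matter, since a marker with wide spread between men can still track closely within each man.
- **That the comparison is biased.** It is shifted only conditionally on an observed imbalance in that marker.
- **That one imbalance pushes the vascular endpoints and the markers in opposite directions.** Section 9.2 does compare FMD and LDF at each time point without the visit 2 value. But the shifts, r × d0 there and -(1 - r) × d0 here, each apply to that variable's own baseline difference. Linking them needs correlations between variables that the protocol does not give.
- **That the estimator decides whether a moderate effect is seen.** At 0.5 SD, power is 18% for the change score against 26% for ANCOVA at r = 0.2, and 26% against 32% at r = 0.5. Either method would usually miss such an effect.
- **That the changes are raw.** Section 9.2 plans transformation for non-normal data. What is missing is baseline adjustment, whatever the scale.

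It is also fair to say that if the markers track at r of 0.8 or more, little is lost.

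**Conclusion.** The point holds as a specific, nearly free gain. The protocol fixes an unadjusted comparison of changes, so this is not detail left to a later analysis plan. In large samples that comparison is less precise than ANCOVA for every r below 1. At 15 per group, after the slope cost, ANCOVA has about 38% less variance at r = 0.2, 22% less at r = 0.5 and 12% less at r = 0.7, with the advantage gone above about 0.9. An ordinary one-standard-error imbalance moves the change comparison by 0.11 to 0.29 SD for r between 0.7 and 0.2, in the direction opposite to the imbalance, and randomisation protects only the smoking classes.

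These sizes rest on an assumed r, equal SDs at the two visits, a linear relation with a common slope, and 15 evaluable men per group. The direction of the precision result does not depend on r until r exceeds about 0.9. Applying the rule to all secondary markers is an inference about intent, because the item numbers in section 9.2 do not match the secondary list.

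**What to change.** In section 9.2, replace the t-test on changes by ANCOVA for each marker: the week-4 value and the week-8 value, each regressed on treatment with the visit 2 value as covariate. Outcome and covariate should be on the same scale, transformed where needed. Report the adjusted difference with a 95% confidence interval, or the adjusted ratio if the scale is logarithmic. Changes from baseline can stay as descriptive figures.

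Reword section 9.3 so that it does not rule this model out. In the same edit, replace the reference to secondary parameters 4 to 6 by the names or correct numbers of the parameters meant.

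The cost is a few sentences and one degree of freedom per test. The visit 2 measurements are already planned, so no new data are needed.

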Therefore, in the present study we aim to address both approaches: (i) the assessment of direct effects of an 8-week intervention with the standardized OPC extract MASQUELIER'S® Original OPCs on macro- and microvascular function a well as on established and validated biomarkers of oxidative stress and inflammation and (ii) the assessment of the OPCs intervention’s effects on long-term disease risk by analyzing gene-expression profiles in the systemic body compartment whole blood. Based on the characteristics given above smokers represent an ideal cardiovascular “at risk” population for the investigation of our projected study objectives. Finally, the study is also intended to serve as a potential model for designing future trials that will allow reliable conclusions on the effects of foods/food components in reducing long-term disease risks and thereby permit scientifically-substantiated “disease risk reduction claims” that meet the criteria of European Regulation 1924/2006/EC on nutrition and health claims made on foods.

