**Secondary Objectives**:

The secondary objectives of the study are to assess the effects of the 8-week intake of 200 mg OPCs on

1. plasma nitrite and nitrate levels.
2. systemic oxidative stress markers such as 8-iso-prostaglandin F2 (PGF2) and TEAC plasma levels, GSH levels in erythrocytes, oxidative DNA damage in lymphocytes and gene expression levels of redox enzymes.
3. systemic inflammation parameters such as plasma levels of hsCRP, fibrinogen, the inflammatory cytokines TNF-, IL-1, IL-6 and IL-8 and their gene expression levels.
4. cytokine levels (TNF‑, IL-6, IL-8 and IL-10) in whole blood stimulated with LPS ex vivo.

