### Secondary study parameters/endpoints

Moreover, the effects of the 8-week supplementation period with daily 200 mg OPCs or placebo will be investigated on the following secondary study parameters:

1. Plasma nitrite and nitrate levels
2. Systemic oxidative stress markers:
   1. Plasma levels of 8-iso-prostaglandin F2 (PGF2)
   2. TEAC plasma levels
   3. GSH levels in erythrocytes
   4. Oxidative DNA damage in peripheral lymphocytes
   5. Gene expression levels of the redox enzymes superoxide dismutase, glutathione peroxidase, catalase, hemeoxygenase-1 in whole blood.
3. Systemic inflammation markers:
   1. Plasma levels of hsCRP
   2. Plasma levels of fibrinogen
   3. Plasma levels of inflammatory cytokines TNF-, IL-1, IL-6, IL-8 and IL-10.
   4. Concentrations of the cytokines TNF-, IL-1, IL-6, IL-8 and IL-10 after ex-vivo stimulation with lipopolysaccharide (LPS) of whole blood.
   5. Gene expression levels of cytokines (e.g. TNF-, IL-1, IL-6, IL-8, IL-10), adhesion proteins (ICAM‑1), and I-kB- in whole blood.

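### Each non-vascular marker is tested at 4 and at 8 weeks against an unadjusted p ≤ 0.05, the tested set is not clearly defined, and the tests carry no exploratory label

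*Protocol*

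**What the plan says.** Under Other study parameters, section 9.2 covers everything outside the vascular measurements. Changes from baseline "will be calculated separately for the 4-week intervention interval and the 8-week intervention interval". Group differences in these changes "will be appraised per study parameter by independent-samples Student’s t-test", with transformation or a Mann-Whitney U-test if normality fails. The decision rule follows: "All tests will be carried out two-sided", and "Statistical significance will be accepted at the 95% confidence level (p ≤ 0.05". No adjustment, testing order or leading time point is given.

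The parameters covered are named in a bracket: "secondary study parameters # 4-6 and other study parameters # 1-4". The secondary list in section 7.1.2 is numbered 1 to 3. The other parameters have six entries in section 2, so entries 5 and 6 (plasma OPCs and blood pressure) fall outside the bracket.

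Section 2 frames the secondary aims at one time point: "The secondary objectives of the study are to assess the effects of the 8-week intake of 200 mg OPCs on" the listed markers. Section 7.1.2 leaves one marker group open-ended: "Gene expression levels of cytokines (e.g". Section 1 gives the gene-expression part a substantive purpose, the intervention's "effects on long-term disease risk by analyzing gene-expression profiles in the systemic body compartment whole blood". Section 4.5 describes the study as a pilot, because no suitable data exist for an FMD or LDF sample size.

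**The concern.** A 0.05 threshold limits the error of one test. Section 9.2 applies it to every marker at two intervals and gives each result the same standing. With dozens of tests, an inert product can be expected to produce a few nominally significant antioxidant, anti-inflammatory or gene-expression differences, and nothing in section 9.2 tells the reader to discount them.

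Three features of the text make this worse:

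- The 4-week change gets the same verdict as the 8-week change, although the objectives ask about 8 weeks.
- The set of tested parameters cannot be read off the document, because the bracket and the list disagree.
- Gene expression is tied to long-term disease risk, which an isolated p ≤ 0.05 among many cannot support.

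The markers form a separate family from FMD and LDF, so settling on one primary vascular contrast would leave the problem unchanged.

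**Working it through.** **The plan's own figure.** The protocol gives no error rate for the marker family. Its only figure is 0.05 per test, two-sided (section 9.2).

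**Count of secondary variables (section 7.1.2).**

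- Nitrite and nitrate: 2
- PGF2, TEAC, GSH, DNA damage: 4
- Redox-enzyme genes: 4
- hsCRP and fibrinogen: 2
- Plasma cytokines: 5
- LPS-stimulated cytokines: 5
- Inflammatory genes (five cytokines, ICAM-1, I-kB): 7, a minimum because the list is open

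Sum: 2 + 4 + 4 + 2 + 5 + 5 + 7 = 29. With two intervals, 29 × 2 = 58 tests.

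**Count on the literal bracket.** No secondary entry is numbered 4 to 6, so only other parameters 1 to 4 remain: 5 lipids + 6 fatty-acid genes + platelet reactivity + arginase = 13. With two intervals, 13 × 2 = 26 tests.

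**Expected false positives when nothing works** = number of tests × 0.05, whatever the correlation.

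- 58 × 0.05 = 2.9
- 26 × 0.05 = 1.3

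**Chance of at least one, all tests independent** = 1 − 0.95^k.

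- k = 58: 1 − 0.95^58 = 94.9%
- k = 26: 1 − 0.95^26 = 73.6%

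**Chance of at least one, with correlation.** The protocol gives no correlations, so they are assumed: 0.5 between a marker's 4-week and 8-week changes, and a common correlation between all markers as shown. The figures come from simulated two-sample t-tests with 15 per group, the evaluable number in section 4.5, and are rounded; repeat runs differ by about a percentage point.

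| Marker correlation | 29 markers × 2 | 13 markers × 2 |
|---|---|---|
| 0 | 94% | 72% |
| 0.5 | 73% | 53% |
| 0.8 | 43% | 33% |

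On the narrow reading the chance is already about 48% at a correlation of 0.6. On the broad reading it falls below one half between about 0.7 and 0.8. If correlation exists only within the seven marker groups above, 58 tests give about 92% at a within-group correlation of 0.3 and about 71% at 0.9.

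**Effect of the second interval.** Testing 8 weeks only on the broad reading leaves 29 tests: 29 × 0.05 = 1.45 expected false positives, and a chance of at least one of about 51% at marker correlation 0.5. Choosing the time point helps but does not remove the problem.

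**The case against.** The strongest defence has four parts.

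1. Multiplicity for secondary biomarkers is commonly left to an analysis plan, and none is at hand. This stands against any complaint that an adjustment scheme is absent. It does not dispose of the point, because section 9.2 itself fixes when significance is accepted.

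2. A reader might infer that the protocol has no ranking and no exploratory status at all. The documents do not support that: section 4.5 calls the whole study a pilot, and endpoints are ranked main, secondary and other. What remains is narrower. The marker tests carry no exploratory label of their own, the ranking does not make any marker test depend on another result, and section 9.2 applies the significance threshold to them regardless.

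3. A reader might count all 29 secondary and some 15 other markers as tested. The bracket does not support this: it leaves out plasma OPCs and blood pressure, and its secondary numbers match nothing. The two readings above are therefore kept apart.

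4. The protocol nowhere says that one significant marker proves an effect, and its language on gene expression is partly tentative. That is fair. The risk lies in how results under this rule would be read, not in a stated decision based on a single marker.

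**Conclusion.** The point holds as a wording and interpretation defect in section 9.2. Under the rule as written, about 2.9 false significant marker results are expected on the broad reading and 1.3 on the literal one when nothing works. The chance of at least one ranges from about 94% down to 43% (broad) or 72% down to 33% (literal) as the marker correlation goes from 0 to 0.8. Every value is far above 5%.

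It is tempting to say flatly that a false marker effect is more likely than not. That depends on assumed correlations: it is fairly robust for 58 tests, since a common correlation near 0.8 across such different assays is unlikely, but fragile for 26 tests. The expected counts do not depend on correlation. All figures assume that no marker is affected. The vascular analysis is not touched by this point.

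**What to change.** Change section 9.2 as follows:

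- Correct the bracket so that it names the secondary and other parameters actually tested.
- Make the 8-week change the comparison of interest, in line with the secondary objectives, with the 4-week change as supportive.
- State that secondary and other parameters are exploratory, reported as between-group differences with 95% confidence intervals, with p-values used descriptively.
- State that isolated results at p ≤ 0.05, including gene expression, generate hypotheses and are not evidence on long-term disease risk. One sentence in section 1 should be aligned with this.

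No extra subjects, samples or measurements are needed, and the wording fits the pilot status in section 4.5. The small cost is that isolated marker results can no longer be called statistically significant.
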